### Inclusion criteria

Pregnant women aged between 15 and 19 years, pregnancy age over 36 weeks, low-risk singleton pregnancy, Iranian citizenship, consent to participate in the study, not having history of any diagnosed mental or chronic diseases undergoing drug treatments, and ability to read and write.

### Exclusion criteria

Unwillingness to continue cooperation during the study, occurrence of high-risk obstetric conditions (e.g., pre-eclampsia, premature birth, hysterectomy, etc.), failure to receive 50% of the intervention for any reason.

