### Research environment

This study will be carried out in selected comprehensive health care centers, obstetrics and gynecology offices, perinatal clinics of hospitals and all places where teen mothers are accessible. The reason for choosing such kind of environment is easy access to teen mothers and includes the majority of cultural and social classes. Considering that the present research is a mixed method study, the type and time of the intervention will be determined based on the findings of the previous stage, but our prediction is that the intervention will start from pregnancy.

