### The implementation method

Based on the opinion of expert panel, a part of the strategies and goals will be determined in the form of an intervention program. After approving the protocol of the study with Ethics Committee, and obtaining the necessary coordination between the authorities of healthcare centers and hospitals, the researcher will implement the designed interventional program. After explaining the aim of the study (by [name]), verbal, and informed consent will be given from the eligible women, and if they agree, they will enter the study and be randomly divided into two groups. For sampling, eligible women will be entered into the study using the convenience sampling method. Then, for randomized assignment, the women will randomly assign either to the trial or control groups based on the table of random numbers that will be generated by Random Allocation Software 2.0. To prevent selection bias, allocation concealment to the trial or control group will be done by a researcher who does not participate in the data collection ([name]).

At first, in the 36th week of pregnancy, a pre-test will be taken from both groups and the average self-efficacy scores will be compared between the two groups. The intervention group received the self-efficacy promotion program and the control group did not receive any intervention. After delivery, their self-efficacy score will be checked between two groups. The type of intervention (e.g., role playing, peer education, home visit, virtual training, and etc.), the time of the program implementation (pregnancy, after childbirth, etc.), the people involved in the program will be determined based on the opinion of the expert panel.

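### Randomised women who receive less than half the programme are excluded, which can happen only in the intervention arm; this breaks the randomised comparison and likely biases the effect upward

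*Protocol article*

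**What the plan says.** The quantitative phase is labelled semi-experimental, but allocation is random. Under The implementation method, consenting women are told that "they will enter the study and be randomly divided into two groups", and "the women will randomly assign either to the trial or control groups based on the table of random numbers" generated by software, with allocation concealed to prevent selection bias. A pre-test is taken at week 36. The intervention group then receives the programme, while "the control group did not receive any intervention". The outcome comparison follows the birth: "After delivery, their self-efficacy score will be checked between two groups".

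The Exclusion criteria for this phase list three events that occur after entry. Two of them can arise in either arm: "Unwillingness to continue cooperation during the study, occurrence of high-risk obstetric conditions". The third is "failure to receive 50% of the intervention for any reason".

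The Data analysis section lists tests and names no analysis population. Sampling method, and sample size leaves the number of women to a pilot study. No section says that an excluded woman is still asked for the post-test or counted in her allocated group.

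**The concern.** Random allocation makes the two groups comparable on everything except the programme. A rule that removes women on something observed after allocation, in one group only, gives up that property. The retained intervention women are a selected group, and the controls are not.

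The selection probably bears on the outcome. The Introduction relies on a theory under which people avoid tasks at which they expect to fail. By that theory, women low in self-efficacy are more likely to miss sessions, and self-efficacy is the score being compared. There is a second route: if the programme helps only those who take it up, dropping those who did not hides the dilution that would occur in practice.

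At stake is the sole stated objective of the fourth phase, the effect of the programme on the self-efficacy score.

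**Working it through.** **No figure to reproduce.** The article states no sample size, SD, effect size, power, expected attendance or dropout. Everything numerical below is an assumption.

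**Step 1: who can trigger the rule.** Randomisation happens at entry, before any exposure. Receipt of half the programme is known only later. Controls are offered nothing, so taken literally every control would meet the criterion. The only workable reading is that it applies to the intervention arm.

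**Step 2: spurious gain when the programme does nothing.** Assume that attendance propensity and the post-test score are bivariate normal with correlation r. The lowest-attending share q of the intervention arm is removed, and no controls are. With z_q the q-quantile of the standard normal and φ its density, the shift in the between-arm difference, in SD units, is

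bias = r × φ(z_q) / (1 − q)

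The multiplier φ(z_q)/(1 − q) is about 0.195 at q = 10%, 0.350 at 20% and 0.497 at 30%. A simulation at q = 20%, r = 0.3 gave 0.105, the same as the formula.

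**Step 3: false-positive rate.** Take n = 50 randomised per arm (assumed), a two-sided 5% test, the normal approximation and no pre-test adjustment:

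SE = √(1/(n(1 − q)) + 1/n), which is 0.205, 0.212 and 0.220 for q = 10%, 20% and 30%

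rate = Φ(bias/SE − 1.96) + Φ(−bias/SE − 1.96)

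| q removed | r | bias (SD) | false-positive rate |
|---|---|---|---|
| 10%, 20% or 30% | 0 | 0 | 5.0% |
| 10% | 0.3 | 0.06 | 5.9% |
| 20% | 0.3 | 0.105 | 7.8% |
| 30% | 0.3 | 0.15 | 10.4% |
| 10% | 0.5 | 0.10 | 7.6% |
| 20% | 0.5 | 0.175 | 13.1% |
| 30% | 0.5 | 0.25 | 20.3% |

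The rate grows with the size of the trial, because the bias does not shrink with n. In the most adverse cell (q = 30%, r = 0.5) it is 14.1% at 30 per arm and 35.7% at 100 per arm. If r were −0.3 the bias would run from −0.06 to −0.15 SD.

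**Step 4: when the programme works.** Assume an effect of 0.5 SD in women who take at least half and none in the rest. The effect across all randomised women is 0.5 × (1 − q) = 0.45, 0.40 and 0.35 SD for q = 10%, 20% and 30%. With r = 0, the analysis after exclusion estimates 0.50 SD in every case. It stays above the all-randomised effect unless r is below about −0.26, −0.29 and −0.30 respectively.

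**Step 5: after the fix.** If every randomised woman is kept in her allocated arm and her outcome is obtained, the bias from this rule is 0 and the false-positive rate is 5%.

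**The case against.** The strongest case against concerns certainty and size, and much of it stands.

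- **Direction.** The article has no data on how attendance relates to self-efficacy, and a rule covering any reason takes in many causes. At r = 0 there is no bias under the null, and a negative r reverses it. A reader might infer that the effect is certainly inflated; the text supports only that this is likely.
- **Pre-test.** Steps 2 and 3 model an unadjusted post-test difference. The plan has a pre-test and lists a paired t-test and repeated-measures ANOVA. If change is compared, and attendance relates equally to both scores with equal variances, the null bias cancels. The article does not fix which comparison is primary, so the table describes one reading. The overstatement in Step 4 at r = 0 remains.
- **Obstetric events and withdrawal.** A reader might infer that these exclusions bias the comparison in the same way. Either arm can trigger them, and nothing shows that the programme changes how often obstetric complications occur. They lose data and narrow the population; between-arm bias is not shown.
- **Early delivery.** It is tempting to argue that women who give birth soon after entry would miss half the programme. That depends on a schedule not yet fixed: Research environment says only that "our prediction is that the intervention will start from pregnancy", and The implementation method leaves timing open, including after childbirth.
- **An unseen analysis plan.** It might define an all-randomised population. But the article does more than stay silent: it states an exclusion, which such a plan would have to contradict.

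**Conclusion.** The point holds for the 50% receipt rule. It excludes randomised women after allocation, it can operate in one arm only, and nothing in the article restores them. The loss of the randomised comparison follows from the text and needs no assumption about direction. That the bias is likely upward is an inference from the plausible link between attendance and self-efficacy and from the hidden dilution.

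The size cannot be computed from the article. For an unadjusted post-test comparison with no true effect, the assumed ranges give a spurious gain anywhere from nil to 0.25 SD and a false-positive rate of about 5% to 20% at 50 per arm. The lower end is close to nominal. It should be settled before enrolment, because post-test scores not collected from dropped women cannot be recovered later.

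**What to change.** 1. Remove the 50% receipt rule as a ground for exclusion from follow-up and analysis.
2. Seek the post-test from every randomised woman unless she withdraws consent, whatever share of the programme she received. Include women with later obstetric events. This concerns data collection only and changes no clinical rule on who continues the programme.
3. Make the primary analysis one of all randomised women in their allocated groups.
4. Report women who received at least 50% only as a secondary per-protocol analysis.

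The cost is some rewording, additional questionnaires and a probably smaller estimated effect. Under the Step 4 assumptions with 30% low receipt, the effect to detect falls from 0.50 to 0.35 SD. That needs about (0.50/0.35)² = 2.0 times as many analysed women for the same power; at 10% low receipt the factor is (0.50/0.45)² = 1.2. The sample size is still to come from the pilot, so it can allow for this, and the pilot can record attendance to inform the allowance.

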#### The fourth phase: implementation of the postpartum self-efficacy promotion program for teen mothers

1.1.Determining the effect of a comprehensive postpartum self-efficacy promotion program on the self-efficacy score of teen mothers**.**

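### Excluding women who receive less than 50% of the programme removes participants after randomisation in the intervention arm only and breaks the randomised comparison, with bias that is probably, but not certainly, upward

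*Protocol article*

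**What the plan says.** All places are in the Protocol article, mostly under the fourth (quantitative) phase.

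- *Exclusion criteria* has three items. Two are "Unwillingness to continue cooperation during the study, occurrence of high-risk obstetric conditions". The third is "failure to receive 50% of the intervention for any reason".
- *The implementation method* says that consenting women enter, and "they will enter the study and be randomly divided into two groups". Allocation is software-generated and concealed.
- The same section describes the arms: "The intervention group received the self-efficacy promotion program and the control group did not receive any intervention".
- On timing, "in the 36th week of pregnancy, a pre-test will be taken from both groups", and the outcome comparison is "After delivery, their self-efficacy score will be checked between two groups".
- The fourth-phase objective is "Determining the effect of a comprehensive postpartum self-efficacy promotion program on the self-efficacy score of teen mothers".
- *Data analysis* lists tests. It does not say which one carries the between-group comparison, and nothing in the article keeps the excluded women in the analysis.

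**The concern.** An exclusion criterion that can be judged only during follow-up is not an eligibility rule; it decides who is counted in the result. This one acts on a quantity that exists in one arm only. Withdrawal and obstetric complications can occur in either group, but a control cannot fail to attend sessions she was never offered. The rule therefore takes a selected subset out of the intervention arm and has no counterpart among controls.

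The selection may lie close to the outcome. The *Introduction* adopts a theory under which people act when they believe they can succeed and hold back when they expect failure. On that premise, mothers with low self-efficacy are the likelier to miss sessions. Removing them raises the intervention mean even if the programme does nothing.

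At stake is the only between-group comparison in the study. Random allocation and concealment are there to prevent selection, and this rule lets it back in after allocation.

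**Working it through.** **No figure to reproduce.** The article gives no sample size, alpha, power, effect size, SD or expected attendance; *Sampling method, and sample size* leaves the number to a pilot. What follows is an illustration on assumed inputs.

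**Assumed inputs.** Outcome SD 1. A share q of the intervention arm falls below 50% receipt, with q = 10%, 20% or 30%. A normal latent attendance score has correlation r with the outcome, with r from -0.3 to 0.5. There are n = 50 or 100 women per arm, tested two-sided at 5%. The other two exclusions are ignored.

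**Step 1: shift under no true effect.** Removing the lowest share q on attendance moves the intervention mean by

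bias = r × φ(z_q) / (1 − q).

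For q = 0.2, φ(z_q) = 0.280 and 0.280/0.8 = 0.350. So r = 0.3 gives 0.3 × 0.350 = +0.105 SD, r = 0 gives 0, and r = -0.3 gives -0.105 SD.

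**Step 2: type I error.** At q = 0.2 and n = 50, SE = √(1/40 + 1/50) = 0.212. The shift is 0.105/0.212 = 0.495 standard errors, and the two-sided error is 7.8%. At n = 100, SE = √(1/80 + 1/100) = 0.15, the shift is 0.70, and the error is 10.8%. The table also allows for the slightly smaller variance among attenders, which changes these to 7.9% and 10.9%.

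| Removed | r = -0.3 | r = 0 | r = 0.3 | r = 0.5 |
|---|---|---|---|---|
| 10% | -0.058 SD; 5.9% / 6.9% | 0; 5% / 5% | +0.058 SD; 5.9% / 6.9% | +0.097 SD; 7.7% / 10.5% |
| 20% | -0.105 SD; 7.9% / 10.9% | 0; 5% / 5% | +0.105 SD; 7.9% / 10.9% | +0.175 SD; 13.6% / 22.5% |
| 30% | -0.149 SD; 10.5% / 16.3% | 0; 5% / 5% | +0.149 SD; 10.5% / 16.3% | +0.248 SD; 21.6% / 38.1% |

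Each cell gives the bias, then the type I error with 50 / 100 per arm. A larger sample does not help: the bias stays the same and the false-positive rate rises.

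**Step 3: simulation check.** With 4,000 trials at q = 20%, r = 0.3 and n = 50, the mean shift was 0.098 SD and the type I error 8.0%. Keeping every randomised woman in her arm gave 5.3%, which is nominal within simulation error.

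**Step 4: pre-test adjustment.** Assume a baseline-outcome correlation of 0.5 and that attendance also correlates 0.3 with the pre-test. The part of the selection that the pre-test does not explain is then 0.3 − 0.5 × 0.3 = 0.15, and 0.15 × 0.350 = 0.05 SD. Simulation gave 0.050 SD and a type I error of 6.6% at n = 50. The shift is about halved, not removed.

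**Step 5: when the programme works.** Suppose receivers gain 0.5 SD, non-receivers gain nothing and q = 20%. The effect in all randomised women is 0.8 × 0.5 = 0.40 SD. Under the rule the comparison shows 0.5 + 0.350r: 0.50 SD at r = 0, about 0.60 SD at r = 0.3, and about 0.40 SD at r = -0.3.

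**The case against.** **Direction.** A reader might infer that the effect is certainly inflated. The documents do not show this. The theory in the *Introduction* makes it likely, but the rule applies whatever the reason for non-receipt. Women enter late in pregnancy, and the format and timing of the programme are still undecided. Delivery before the sessions are complete, or plain logistics, could cause non-receipt with little relation to confidence. At r = 0 there is no bias under the null, and if confident mothers skip sessions the sign reverses. This objection stands, and the direction is put here as probable only.

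**Who is left in the control group.** It is also tempting to say that attenders are compared with all controls. That is not right, because the other two exclusions can remove controls too. The accurate statement is that the remaining controls are not selected on attendance. The literal reading, under which the rule would exclude every control because none receives the programme, is plainly not intended and adds nothing.

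**Size.** The inputs are assumptions, and the type I errors are for an unadjusted post-test comparison although a pre-test is taken. Adjustment reduces the bias (Step 4). A comparison of change scores would cancel the shift under the null if attendance related equally to pre-test and post-test, since 0.3 − 0.3 = 0. It would still report the gain in receivers rather than in all women offered the programme. The article commits to neither analysis. So the unadjusted figures lie towards the unfavourable end, but they do not go away.

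**An analysis plan might settle it.** A plan that is not at hand could analyse everyone as randomised. It would then contradict a rule the article states outright, and the rule would still need correcting. Calling the design semi-experimental, as *Type of quantitative study* does, does not help either, because allocation is described as random.

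**Conclusion.** The point holds as a defect in what is written: a post-randomisation exclusion that can act in one arm only, applied before the single between-group comparison. That the randomised comparison is broken does not depend on any assumed number.

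The size and sign of the bias do. With 20% removed, correlations of -0.3, 0 and 0.3 give -0.105, 0 and +0.105 SD in an unadjusted post-test comparison under no true effect, with type I error of about 8% (50 per arm) or 11% (100 per arm) at either non-zero value. Adjusting for the pre-test roughly halves the shift if baseline and outcome correlate 0.5 and attendance relates equally to both. A reader might go further and say that a positive result would be selection alone. The documents give no attendance rate, SD or sample size, so they cannot support that. What can be said is that, with the rule in place, selection could not be ruled out as an explanation.

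**What to change.** 1. Delete the 50% rule from *Exclusion criteria*. State that every randomised woman is asked for the post-test and analysed in her allocated arm, whatever share of the programme she received.
2. Reword the other two items so that they do not contradict this. Women with obstetric complications after entry stay in the analysis set, and women who withdraw consent are handled as missing data. This concerns the analysis set only, not clinical care. Withdrawal also needs attention because only one arm carries the burden of a programme.
3. Report receipt of at least 50% as a fidelity measure. If the effect in receivers is wanted, give it as a supplementary complier-average estimate with randomisation as the instrument, not by deleting women.

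**Cost.** The text change is small; the consequences are larger. Non-attenders must be approached for the questionnaire. The estimate will probably be smaller: in the example with a 0.5 SD gain in receivers, 20% non-receipt and r = 0.3, it falls from about 0.60 to 0.40 SD, roughly one third. The pilot-based sample size should use the effect in all randomised women. If that is 80% of the receivers' effect, the required number is 1/0.8² = 1.56 times what the receivers' effect alone would suggest.

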### Study variables

In this study, the designed interventions are considered as an independent variable, and postpartum self-efficacy is considered to be the dependent variable. Variables affecting self-efficacy will be determined using different constructs of Bandura’s self-efficacy theory (e.g., including successful experiences of the individual, social modeling, social persuasion, and psychological responses), and based on the results of a qualitative study and scoping review, different areas of self-efficacy (e.g., self-efficacy in self-care, infant care, breastfeeding, etc.) will be determined.

### Data collection method

Researcher-made questionnaires evaluating postpartum self-efficacy in adolescent mother will be applied in the quantitative phase of this trial. After qualitative interview and searching in existing questionnaire, the validity and reliability of this questionnaire will be determined. In order to assess the content and face validity, the scale will be given to 15 faculty members of the midwifery, gynecology, and psychology department, and their expert’ opinions will be qualitatively received and the suggested changes will be applied in the questionnaire. In order to check face validity, the questionnaire will be provided to a number of women with the characteristics of the research units. The reliability of the tool will be done by test–retest method and the internal correlation will be evaluated with Cronbach’s alpha test.

### The implementation method

Based on the opinion of expert panel, a part of the strategies and goals will be determined in the form of an intervention program. After approving the protocol of the study with Ethics Committee, and obtaining the necessary coordination between the authorities of healthcare centers and hospitals, the researcher will implement the designed interventional program. After explaining the aim of the study (by [name]), verbal, and informed consent will be given from the eligible women, and if they agree, they will enter the study and be randomly divided into two groups. For sampling, eligible women will be entered into the study using the convenience sampling method. Then, for randomized assignment, the women will randomly assign either to the trial or control groups based on the table of random numbers that will be generated by Random Allocation Software 2.0. To prevent selection bias, allocation concealment to the trial or control group will be done by a researcher who does not participate in the data collection ([name]).

At first, in the 36th week of pregnancy, a pre-test will be taken from both groups and the average self-efficacy scores will be compared between the two groups. The intervention group received the self-efficacy promotion program and the control group did not receive any intervention. After delivery, their self-efficacy score will be checked between two groups. The type of intervention (e.g., role playing, peer education, home visit, virtual training, and etc.), the time of the program implementation (pregnancy, after childbirth, etc.), the people involved in the program will be determined based on the opinion of the expert panel.

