### Data analysis

The data analysis will be done using SPSS software ver. 16 by descriptive, and inferential statistics including paired t-test, repeated measure ANOVA, Chi-squared test, Fishers exact test, ANOVA, Wilcoxon test, and Mann–Whitney test.

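### A postpartum self-efficacy questionnaire is also given before birth, so a within-arm change from pre-test to post-test cannot be read as a programme effect

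*Protocol article*

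**What the plan says.** All references are to the protocol article; the trial is its fourth phase.

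- **Outcome.** *Study variables* states that "postpartum self-efficacy is considered to be the dependent variable". It adds that "different areas of self-efficacy (e.g., self-efficacy in self-care, infant care, breastfeeding, etc.) will be determined" from the qualitative study and the scoping review.
- **Instrument.** *Data collection method*: "Researcher-made questionnaires evaluating postpartum self-efficacy in adolescent mother will be applied in the quantitative phase of this trial". No separate antenatal form or wording is named.
- **Questionnaire checks.** The same section plans expert review, face validity, test-retest reliability and Cronbach's alpha. For face validity, "the questionnaire will be provided to a number of women with the characteristics of the research units".
- **Entrants.** *Inclusion criteria* of the fourth phase: "Pregnant women aged between 15 and 19 years, pregnancy age over 36 weeks". Parity is not restricted.
- **Timing and use.** *The implementation method* says that "in the 36th week of pregnancy, a pre-test will be taken from both groups" and that mean scores are compared between the groups. After delivery the scores are again compared between the groups. Allocation is random.
- **Analysis.** *Data analysis* lists methods that include "paired t-test, repeated measure ANOVA", without tying any of them to a contrast.

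**The concern.** A paired t-test, or the time term of a repeated-measures ANOVA, treats the two scores as one quantity on one scale. Here the two administrations fall on either side of the event that the items are about. A woman expecting her first child can only predict how confident she will be in feeding or caring for an infant. A woman with an earlier child answers from experience. After delivery, all of them do.

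The protocol's own text gives reasons to expect scores to move without any programme. The *Introduction* lists a person's own successful experiences and psychological responses among the sources of self-efficacy. A first-time mother has no experience of caring for her own infant at week 36 and does have it later. The *Discussion* reports that perceived stress is much higher after childbirth than in pregnancy. The direction of the net movement is not known.

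What is at stake is a mistaken claim of effect. A significant paired test in the intervention arm could be reported as success when it reflects only the passage from expectation to experience. A fall in scores could equally hide a benefit.

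**Working it through.** **Figures in the plan.** The article gives no effect size, SD, pre-post correlation or sample size (the last is left to a pilot study), so there is no stated figure to reproduce. Everything below rests on assumed values and shows only how each test behaves.

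**Step 1: false-positive rate when the programme does nothing.** Assumptions: scores with SD 1 at both times; a shift s between the pre-birth and post-birth score, the same in both arms; pre-post correlation r of 0.2 or 0.6; 30 or 60 women per arm; two-sided 5% level; 4,000 simulated trials per setting.

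For the within-arm paired test, the expected t is about s√n / √(2(1−r)). With n = 30, r = 0.2 and s = 0.3 this is 0.3 × 5.477 / 1.265 = 1.30, although the programme effect is zero. It grows with n and with r.

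Share of runs in which the within-arm paired t-test is significant:

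| n per arm | r | s = 0 | s = 0.3 SD | s = 0.5 SD |
|---|---|---|---|---|
| 30 | 0.2 | 5.4% | 24.3% | 54.7% |
| 30 | 0.6 | 4.5% | 42.9% | 84.8% |
| 60 | 0.2 | 4.8% | 44.4% | 85.9% |
| 60 | 0.6 | 4.4% | 73.0% | 99.1% |

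In the same runs:
- between-arm t-test of the post-delivery score: 4.3% to 5.2% in every setting;
- between-arm t-test of change, which equals the group-by-time test with two time points: 4.7% to 5.65% in every setting.

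A shift common to both arms cancels between the arms. It does not cancel within an arm.

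**Step 2: precision.** With equal variances, Var(change) / Var(post) = 2(1−r). If the pre-test is used as a covariate, the residual variance relative to Var(post) is 1−r².

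| r (assumed) | Change: 2(1−r) | SE ratio √(2(1−r)) | Covariate: 1−r² |
|---|---|---|---|
| 0.2 | 1.6 | 1.26 | 0.96 |
| 0.4 | 1.2 | 1.10 | 0.84 |
| 0.5 | 1.0 | 1.00 | 0.75 |

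A between-arm analysis of change therefore has a standard error about 26% larger than the postpartum score alone at r = 0.2, about 10% larger at r = 0.4, and no larger at r = 0.5. Above 0.5, change is the less variable of the two. Covariate adjustment is never worse than either in this formula, since 1−r² ≤ 1 and 1−r² = (1−r)(1+r) ≤ 2(1−r).

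**The case against.** The case on the other side is substantial.

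- **The scores may be comparable.** A reader might infer that pre-test and post-test simply do not measure the same thing. The documents do not establish that. The questionnaire is not yet written, its areas are still to be settled, and the *Introduction* treats self-efficacy as a belief that one can do something, which can be held before the task arises. What stands is narrower: the two uses are treated as comparable, and no wording or check for both stages is stated.
- **The comparisons described are between groups.** *The implementation method* compares the arms at each time point and nowhere calls within-woman change the effect. The within-arm reading is only implied by the list of tests. This stands. It limits the point to those listed tests, and the proposed primary contrast is close to what that section already describes.
- **Randomisation protects the main result.** A reader might infer that the trial's effect estimate is biased. Step 1 shows that it is not under a common shift. The group-by-time term of the repeated-measures ANOVA keeps its error rate too; only the within-arm paired test, and by the same logic the time term, are affected.
- **The programme could change how women rate themselves.** That would distort the postpartum score as well, so it is a general limit of self-report and no argument for one contrast over the other. The documents give no evidence that it would occur.
- **The validation sample.** A reader might infer that the scale will never be checked in postpartum mothers. The article does not say whether those women are pregnant or postpartum, and trial participants are in both states during the study. All that can be said is that a check in both states is not stated.

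**Conclusion.** The point holds in a limited form. One questionnaire, described only as a postpartum measure for mothers, is used before and after birth, and the listed tests include one that reads the difference within an arm. That difference mixes the move from expectation to experience with any programme effect, so it is not evidence that the programme works. Under the assumed shifts of 0.3 to 0.5 SD, the within-arm test gives a significant result in about 24% to 99% of trials of an ineffective programme. The size of any real shift is not known from the documents.

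The randomised comparison of postpartum scores and the group-by-time test remain valid as long as the shift is common to both arms. Any loss of precision from using change depends wholly on the assumed correlation: about 26% in standard error at r = 0.2, and none at r = 0.5. It is a secondary matter.

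The change is worth making now because the questionnaire is still to be written. Once the week-36 form has been given, its wording cannot be repaired.

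**What to change.** 1. In *Data analysis*, state that the programme effect is the between-arm difference in the postpartum score, adjusted for the pre-test as a baseline covariate.
2. State that within-arm paired tests are not used as evidence of effect. If they are shown at all, label them descriptive.
3. In *Data collection method*, word the week-36 items as anticipatory confidence (how confident the woman is that she will be able to do the task). Record parity at entry.
4. Run the face-validity, test-retest and Cronbach's alpha checks already planned in both pregnant and postpartum teens, each with the form that group will receive.

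Cost: some questionnaire wording, one extra baseline item, and a validation sample split into two groups, so each check rests on fewer women unless the sample is enlarged. Within-arm change is no longer reported as an effect. The randomised design and the assessment times stay as they are.
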